Plan for AIDS Relief (PEPFAR) via the Center for Disease Control (CDC). FACES began services in March 2005 in Nyanza Province and is a collaboration between the Kenya Medical Research Institute (KEMRI) and the University of California, San Francisco (UCSF). FACES' mission is to provide accessible comprehensive care and support services to HIV affected families and other vulnerable populations, reinforce prevention practices, and build capacity related to HIV/AIDS care. FACES partners with government health facilities to provide HIV care, treatment, and support to individuals and families in the Nyanza province and currently has over 13,000 patients enrolled in care and over 3,000 on antiretroviral therapy (ART). The Nyanza province has the highest HIV prevalence in Kenya, with 18.3% of women and 11.6% of men aged 15-49 estimated to be infected in 2003[15]. FACES data suggests that contraception prevalence ranges somewhere between 23-35 percent[17]. Because family planning services are not currently provided in an integrated manner within the care facilities that FACES currently works in or those where it will expand to within the 2007-2009 fiscal years in Suba, Kisumu East, Rongo and Migori Districts, this setting affords an excellent opportunity to study the effect of integration on critical indicators of contraceptive use.

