## **STATISTICAL/ANALYSIS PLAN**

### **Sample size considerations**

**Data abstracted from clinical encounter forms.** We have used ACLUSTER program to generate the number of PSC pairs (or clusters) that we will need to assess changes in contraceptive prevalence and unintended pregnancy. The first input into this program is the size of each cluster (or the number of eligible subjects available at each PSC site). There are a total of 36 FACES-supported PSC sites in Migori, Rongo, Kisumu East and Suba Districts, which are not all equal in size. The first calculation takes into account how we determine the average number of non-pregnant females of reproductive age that are potentially recruitable at each site. The other main input is the desired effect size we aim to be able to measure. Additional inputs include alpha, power and the Intra-cluster Correlation Coefficient (a measure of how similar we expect the two sites in each paired cluster to be to each other, for which we selected an intermediate value). Based on this we need 18 sites, 12 with the intervention and 6 control to be able to evaluate the integration model we propose as described in more detail below.

For the main cluster-randomized trial, the following data were inputted into the ACLUSTER program to generate an estimated number of clusters needed:

- 1. Number of subjects per cluster or site
  - a. The eligible sample includes all FACES-supported PSCs in Suba, Kisumu East, Rongo and Migori Districts. The enrollment in December 2007 at the 16 FACES-supported sites in Suba District was 10,280, at the four sites in Kisumu was 6,593, at the five sites in Rongo was 1,338, and at the 11 FACES-supported sites in Migori District is 4,882.

- b. Because there are not accurate data about the number of non-pregnant women of reproductive age at these sites, we applied estimates based on observations of client demographics at the FACES site in Kisumu, where 65% of all clients are adult females, 89% of the female population is of reproductive age, and 90% of the reproductive age females are not pregnant.
  - c. Applying these estimates, our eligible sample is approximately 12,023 women at 36 sites, an average of 333 women per site. For the sample size calculation, a conservative estimate of approximately 200 eligible women per site was used to allow for inclusion of smaller sites.
- 2. Effect size on primary outcome.

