  - a. The primary outcome upon which we based our sample size calculation is contraceptive prevalence. According to the 2003 Kenya Demographic and Health Survey, approximately 22% of women in a union in Nyanza Province use a modern contraceptive method. This level of contraceptive prevalence is similar to that seen among clients at the FACES sites. We would like to be able to detect a 8% rise in contraceptive prevalence to 30%.
- 3. Assumptions
  - a. Two-sided alpha of 0.05
  - b. Power of 0.8
  - c. Intra-cluster Correlation Coefficient of 0.01
- 4. Sample size.
  - a. Using these estimates, the needed sample size is approximately 140 women at each of the 18 sites, for a total sample of 2,520 women.
  - b. We plan to initially recruit a similar number, 2,520, of male clients, however our primary outcome for men will be the proportion of male clients who report they or their partner are interested in starting a new FP method after receiving FP counseling during their visit. In order to accurately calculate this sample size, baseline data is needed to estimate the baseline proportion of male clients who would express interest in starting a new FP method. Thus, after the baseline data collection phase a more accurate sample size for male clients will be calculated.

**KAP surveys.** Because the largest sample sizes are required for expected proportions nearer to 0.5 than to 0 or 1, we will take the worst-case scenario and assume that for each individual question on the survey approximately half of the participants will answer correctly. We hypothesize that people in the intervention sites will be more knowledgeable after the intervention at the end of the study, so we would like to test for at least a ten percentage point difference in correct answers among patients in the intervention sites (~60% correct) compared to patients in the comparison sites (~50% correct), as well as a 10% increase in correct answers among patients in the intervention sites compared to the baseline results. For a one-sided test of two proportions using two samples, power of 0.8, and an alpha level of 0.05, the required sample size is 325 patients from the intervention sites and 163 patients from the comparison sites for both men (N=488) and women (N=488).

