### **Data analysis plan**

Analyses of data from the study health facilities, given the randomized cluster design, will mainly be conducted at the cluster (health facility) level. Individual level analyses will take into account

cluster effects. Primary analyses will be based on the “intention to treat” (ITT) principle, with facilities randomized to the intervention group classified as delivering “integrated services” regardless of whether or not individual women actually received integrated services.

Preliminary analyses will be conducted to compute study outcome variables and to summarize characteristics of control and treatment sites to assess the effectiveness of randomization. Initial analyses also will involve inspection of the frequency distributions of variables to identify outlying or unusual values. Following univariate descriptions of the data, bivariate and multivariate associations will be assessed as described below.

Analysis of the primary outcomes, contraceptive prevalence and unintended pregnancy rates, and the secondary outcomes, acceptability of services and knowledge related to contraception, will be based on a comparison of means or proportions between study arms using a weighted t-test that accounts for correlations between individual outcomes within sites. Even though there are only 12 health facilities in the intervention arm and 6 health facilities in the comparison arm, each mean or percentage will be based on a relatively large number of women, and the normal approximation to the binomial distribution can be used. These tests will be evaluated based on a two-sided alternative hypothesis, 80% power, and a 5% type I error rate. The same basic approach will be used for the other primary and secondary outcomes. Results will be summarized as odds ratios for models based on binary responses (e.g. use of contraception or experiencing unintended pregnancy), and mean changes for continuous responses (e.g. score on knowledge test).

As noted above, All open-ended interviews will be tape recorded (if the woman gives informed consent), transcribed, translated to English. A content analysis will be performed using the qualitative software ATLAS.ti in order to describe themes in women’s experiences undergoing contraceptive counseling, receiving family planning methods and in the acceptability of these services.

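### At the stated 140 women per site, 80% power holds only under a normal approximation; the planned t-test on 12 and 6 sites has about 76%, less at a higher baseline

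*Protocol*

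**What the plan says.** All references are to the Protocol.

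- **Sample size considerations, items 2 to 4.** The inputs are "Two-sided alpha of 0.05", power 0.8, "Intra-cluster Correlation Coefficient of 0.01", and a rise from 22% to 30%. The result is that "the needed sample size is approximately 140 women at each of the 18 sites, for a total sample of 2,520 women".
- **Sample size considerations, opening text.** The program is said to give a number of site pairs, and the ICC is described as "a measure of how similar we expect the two sites in each paired cluster to be to each other". The same text gives 12 intervention and 6 control sites, an average of 333 eligible women per site, and a conservative 200 used for the calculation.
- **Baseline.** Item 2a takes "approximately 22% of women in a union in Nyanza Province use a modern contraceptive method" and adds: "This level of contraceptive prevalence is similar to that seen among clients at the FACES sites". The Background section says: "FACES data suggests that contraception prevalence ranges somewhere between 23-35 percent".
- **Randomisation** (Overview; Part II; Potential Design Pitfalls). Sites fall into two strata, with six intervention and three control sites drawn from each. There are no pairs.
- **Data analysis plan.** The primary outcomes are compared by a weighted t-test that allows for correlation within sites. The text acknowledges that there are only 12 and 6 facilities, but says that each mean or percentage is "based on a relatively large number of women, and the normal approximation to the binomial distribution can be used". It then states 80% power and a 5% type I error rate.

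**The concern.** In a cluster-randomised trial, the arm difference is judged against variation between sites, and that variation is estimated here from 18 values. Many women per site make each site's percentage more precise and closer to normal, but they do not make 18 sites a large sample. The reference distribution is therefore t on roughly 16 degrees of freedom. A size calculation that uses normal critical values overstates the power of that test.

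Two further weaknesses affect the inputs. The ICC is the correlation between women at the same site, not the likeness of two sites in a pair, and no source is given for 0.01. The 22% baseline lies below the whole range that the protocol reports for the programme's own clients. A higher baseline means a larger binomial variance for the same 8-point difference.

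At stake are how a null result would be read and, if the normal-approximation sentence were taken as licence to use 1.96, the error rate and the width of the confidence intervals.

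**Working it through.** **Inputs from the protocol:** p0 = 0.22, p1 = 0.30, ICC = 0.01, two-sided alpha 0.05, 12 intervention and 6 control sites, m = 140 women per site. Equal site sizes are assumed throughout.

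**1. Reproducing the stated figure**

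- Design effect = 1 + (140 − 1) × 0.01 = 2.39.
- Women per arm: 12 × 140 = 1,680 and 6 × 140 = 840.
- SE = √[2.39 × (0.30 × 0.70/1,680 + 0.22 × 0.78/840)] = √[2.39 × (0.000125 + 0.000204)] = 0.0281.
- 0.08/SE = 2.852.
- Normal-approximation power = Φ(2.852 − 1.960) = 81.4%. With the variance pooled under the null it is 79.3%.
- Solving for m at 80% gives 129 (unpooled) to 146 (pooled). The stated 140 lies between them.

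So 140 × 18 fits an unpaired 12:6 design with an ordinary within-site ICC and normal critical values. An equal 9:9 split with t on 16 df also gives about 80% (79.7%), so the text does not settle which calculation was run.

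**2. Power of the planned t-test at 140 per site**

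The degrees of freedom are 12 + 6 − 2 = 16 and the critical value is 2.120. A noncentral t with noncentrality 2.852 gives 76.3%. Variants:

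- 15 df, allowing one for the strata: 76.0%
- Satterthwaite: 73.9%
- pooled SE: 73.2%
- beta-binomial simulation, 100,000 replicates: 74.2%

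**3. Cluster size**

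| Women per site | Design effect | t(16) power, 22% vs 30% |
|---|---|---|
| 140 | 2.39 | 76.3% |
| 178 (3,204 in total) | 2.77 | 80% |
| 200 | 2.99 | 81.6% |
| 333 | 4.32 | 86.6% |

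At 200 per site, the Satterthwaite and pooled-SE variants give 79.3% and 78.7%.

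**4. Baseline, with an 8-point rise and ICC 0.01, t(16)**

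| Baseline | 140 per site | 200 per site |
|---|---|---|
| 22% | 76.3% | 81.6% |
| 23% | 75.2% | 80.6% |
| 29% (midpoint of 23-35%) | 69.9% | 75.5% |
| 35% | 66.3% | 72.0% |

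**5. Type I error if 1.96 is applied to 18 site values**

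P(|t16| > 1.96) = 6.8%. Simulation under the null (22% in both arms) gives 6.8% with 1.96 and 5.0% with the t reference.

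**6. Sensitivity to the ICC**

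The protocol gives only 0.01; the other values are assumptions. At 22% versus 30% and 140 per site, t(16) power is 88.8% at ICC 0.005, 76.3% at 0.01, 56.8% at 0.02 and 44.5% at 0.03. At 200 per site and ICC 0.02 it is 60.2%.

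**The case against.** The strongest reply is that 140 is a needed minimum. The Endpoints section takes the primary outcomes from the encounter forms of all HIV-positive clients, and the protocol calls 200 eligible women per site conservative against an average of 333. On those numbers the t-test reaches 80% at the 22% baseline. This largely stands: a reader might infer that the trial will have only 76% power, and the protocol does not support that. Two limits apply. Abstraction requires signed consent, and the protocol says that sites differ in size. Both would lower power, by amounts for which it gives no data.

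A reader might also infer that the pairing language and the ICC definition produced a wrong sample size. Step 1 shows otherwise: the figure reproduces without pairs and with the usual ICC. They are errors of description.

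Nor is power 66-70% across the programme's own baseline. That covers only 29-35%. At 23% the loss from 22% is about one point. The cited source for the range is titled as data from one place, Lumumba, and it speaks of contraception where the 22% refers to modern methods, so the two measures may differ. They still need reconciling.

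Finally, the plan names a t-test and never says that 1.96 will be used. The normal-approximation sentence can be read as describing each site's percentage only. The 6.8% is therefore conditional. What remains wrong is the reasoning: it offers the number of women as the answer to the small number of sites.

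**Conclusion.** The point holds in limited form, and the text should be fixed. At the stated 140 women per site, the 12:6 design analysed by the planned t-test has about 76% power (73-76% by variant), not 80%. The shortfall of about 4 points comes from ignoring the site-level degrees of freedom. At 200 per site power is about 82%. Over the protocol's 23-35% range it runs from 75% down to 66% at 140 per site, and from 81% down to 72% at 200. These figures assume equal site sizes, an 8-point difference and ICC 0.01. The unsupported ICC matters more than the t correction: doubling it to an assumed 0.02 leaves 57% at 140 per site. The 5% error rate is at risk only if normal critical values are applied.

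**What to change.** 1. Restate power for the unpaired 12:6 design with t inference: about 76% at 140 women per site and about 82% at 200, with equal site sizes stated as an assumption.
2. Define the ICC as the correlation between women within a site, and delete the references to pairs.
3. Replace the normal-approximation sentence with t inference on site-level degrees of freedom (about 16, or 15 allowing for the strata).
4. Reconcile the 22% baseline with the 23-35% in the Background section, stating whether both refer to modern methods and to the same clients.
5. Use the Part I data, collected at all 18 sites before randomisation, to re-estimate baseline and ICC, and then restate the detectable difference. Item 4b already plans a recalculation after baseline for men; extend it to women. Show sensitivity to other ICC values, labelled as assumptions.

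The cost is some rewording and one calculation on data that will be collected anyway, with no added enrolment. The downside is that the stated power becomes slightly less favourable.

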## **1. Part I: Baseline data collection (Months 1-3)**

### **1.1. Baseline site-based data collection**

During a period of three months, baseline quantitative data on contraceptive prevalence, contraceptive methods used and pregnancy (including degree to which pregnancy was planned and desired) will be collected as part of routine clinical care at the 18 sites in Suba, Kisumu East, Rongo and Migori Districts. This information will be collected in a standardized clinical encounter form from all HIV-positive women age 18-45 at the time of each visit to the site. Data will also be collected on HIV-positive men age 18-45 regarding condom use, vasectomy and partner's use of other methods. A draft of the questions that will be used to collect the site-based data is included in Appendix A.

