## 2.2 Intervention implementation

After the intervention is fully designed, it will be implemented at twelve “intervention” FACES-supported PSC’s using a model that will ultimately include integrating HIV and FP services in all 18 sites. Implementing the intervention will consist of:

- Training clinic staff in family planning counseling and method provision
- Introducing family planning assessments into all clinic visits via incorporating inquiries as to family planning needs on all medical forms, thereby prompting provider questioning
- Introducing new client counseling sessions and education materials into the PSC care infrastructure
- Devising a system of procuring, inventorying and dispensing contraceptive methods, including at the very least condoms, oral contraceptives and injectables. At sites where it is feasible, IUDs and implants will also be made available. When a method is not available at the site (such as in the case of surgical sterilization), clients will be referred to nearby centers that offer the method.

At both the intervention and control sites, a brief family planning module will be integrated into the standardized clinic encounter form that is used at each client visit. This module will prompt the clinician to ask if the client is currently using contraception and his or her fertility intentions. Simply put, if the client is using a method, the provider will be ask if he or she is interested in changing the method; if the client is not using a method and does not desire pregnancy, the provider will be ask if he or she is interested in starting a method.

- At “intervention” sites clients will then be extensively counseled about contraception and will be provided any needed contraceptive methods on site.
- At “control” sites, clients will be provided with contraceptive services through the centers’ standard mechanisms, which generally involve referral to an affiliated family planning program that may or may not be on-site.

Prior to implementation of our intervention, we will resubmit the protocol for review at SSC/ERC for review of the final design of any educational materials developed.

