### **3. Part III: Post-intervention data collection (Months 7-15)**

#### **3.1. Post-intervention site-based data collection**

Over the following nine months, data on contraceptive prevalence, contraceptive methods used and pregnancy (including degree to which pregnancy was planned and desired) will be collected, as part of routine care, at the 18 sites (twelve intervention and six control sites) among women age 18-45 and men age 18 and older. Data will also be collected on whether contraceptive counseling was performed at each clinic visit. This information will be collected in the standardized clinic encounter form from all HIV-positive women and men at the time of each visit to the site. At each of the sites, a random sample of 10-15% of all charts will be reviewed during the post-intervention period to determine if the family planning module of the clinical encounter form is being filled out. A draft of the questions that will be used to collect the site-based data is included in Appendix A.

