### **ENDPOINTS**

**Primary Outcomes** (data abstracted from clinic encounter forms from all HIV-positive clients):

1. Contraceptive prevalence
  - a. Will compare post-intervention data from intervention sites to data collected over same time period from control sites
2. Pregnancy rate (number of pregnancies/number of unique clients seen during post-intervention data collection period) and percent of pregnancies that are unplanned
  - a. Will compare post-intervention data from intervention sites to data collected over same time period from control sites

**Secondary Outcomes** (data collected from KAP surveys and in-depth interviews):

1. Knowledge of contraceptive methods among HIV-positive clients
  - a. Will compare pre-intervention rates from baseline data to post-intervention data at intervention sites

- b. Will compare pre-intervention rates from baseline data to post-intervention data at control sites
  - c. Will compare post-intervention data from intervention sites to data collected over same time period from control sites
- 2. Knowledge of contraceptive methods among providers, including peer counselors, at HIV care and treatment centers
  - a. Will compare pre-intervention rates from baseline data to post-intervention data at intervention sites
  - b. Will compare pre-intervention rates from baseline data to post-intervention data at control sites
  - c. Will compare post-intervention data from intervention sites to data collected over same time period from control sites
- 3. Acceptability of family planning services
  - a. Will compare pre-intervention rates from baseline data to post-intervention data at intervention sites
  - b. Will compare pre-intervention rates from baseline data to post-intervention data at control sites
  - c. Will compare post-intervention data from intervention sites to data collected over same time period from control sites
- 4. Feasibility of providing family planning services at HIV care and treatment centers (data from post-intervention surveys of clinic staff)
- 5. Reproductive intentions of HIV-infected clients receiving care and treatment (data from baseline client surveys and in-depth interviews)

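### The men's primary outcome is tied to counselling, which is part of the intervention, has no fixed denominator, and conflicts with the endpoint list, so it gives no clean comparison of the arms

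*Protocol*

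**What the plan says.** Sample size considerations, item 4b, defines the primary outcome for men as a proportion, counting "male clients who report they or their partner are interested in starting a new FP method after receiving FP counseling during their visit". No denominator is given beyond male clients. The number of men is provisional ("We plan to initially recruit a similar number, 2,520, of male clients"), and "after the baseline data collection phase a more accurate sample size for male clients will be calculated".

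Other sections bear on the same outcome:

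- **Endpoints.** The primary outcomes are contraceptive prevalence and pregnancy, from "data abstracted from clinic encounter forms from all HIV-positive clients". Interest in starting a method is not listed. The Data analysis plan, where it names the primary outcomes, also omits it.
- **Abstract, objective 1.** The aim is the effect of integration on family planning utilization by women and men.
- **Section 2.2.** A common module at both intervention and control sites has the provider ask about interest: users about changing method, and non-users who do not desire pregnancy about starting one. At intervention sites "clients will then be extensively counseled about contraception and will be provided any needed contraceptive methods on site". Control clients go through the site's standard mechanism, generally referral.
- **Potential benefits.** Contraceptive counselling is described as not currently part of standard HIV care.
- **Section 1.1 (baseline).** "Data will also be collected on HIV-positive men age 18-45 regarding condom use, vasectomy", together with partner's use of other methods.
- **Section 3.1 (follow-up).** Data are collected "among women age 18-45 and men age 18 and older". The consent text for site-based data, headed as covering baseline and post-intervention, takes men aged 18 and above.

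**The concern.** A randomised comparison needs an outcome that can be assessed in the same way in both arms. Receipt of counselling happens after randomisation, and the intervention is designed to change it. An outcome that exists only after counselling therefore mixes two things: who gets counselled, and what counselled men then say.

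There is a second problem of direction. Interest in a new method is not use. If integration works and more couples already use a method, fewer men remain to be asked about starting one.

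At stake is whether the male result can be read as benefit or harm at all. The recalculated male sample size is also affected. Item 4b describes the baseline proportion needed for it as men who would express interest, with no counselling condition, so the baseline quantity and the follow-up outcome are not the same.

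**Working it through.** **The plan's own figure.** The only worked sample size is for women: "the needed sample size is approximately 140 women at each of the 18 sites, for a total sample of 2,520 women". Inputs from the same section are 22% versus 30%, two-sided alpha 0.05, power 0.8, intra-cluster correlation 0.01, and 12 intervention and 6 control sites.

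- Two proportions at 2:1 (pooled variance, no continuity correction): 358 control + 716 intervention = 1,074.
- Design effect: 1 + (140 - 1) × 0.01 = 2.39.
- Total: 1,074 × 2.39 = 2,567, against 2,520 stated (1.9% apart). Power at 2,520 is 79.3%.

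The women's figure reproduces. The men's 2,520 is borrowed from it; no rate, effect size or power is given for men, so there is no male calculation to check.

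**Effect of the denominator.** The protocol gives no interest or counselling rates for men in the trial, so all inputs here are assumptions. Let 30% of men be motivated (60% interested) and 70% not (20% interested). Interest among all men is then 0.30 × 0.60 + 0.70 × 0.20 = 32%. Let 80% of intervention men be counselled regardless of motivation, and vary who is counselled in control.

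| Control counselling, motivated / other (overall) | Interested among counselled control men | Reading A: observed difference for a true 0 / +5 / +10 points | Reading B: control vs intervention, no true difference |
|---|---|---|---|
| 60% / 10% (25%) | 48.8% | -16.8 / -11.8 / -6.8 | 12.2% vs 25.6% (+13.4) |
| 40% / 11.4% (20%) | 44.0% | -12.0 / -7.0 / -2.0 | 8.8% vs 25.6% (+16.8) |
| 20% / 20% (20%) | 32.0% | 0 / +5 / +10 | 6.4% vs 25.6% (+19.2) |

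Reading A keeps counselled men only. Reading B keeps all men and counts the uncounselled as not interested. For the first row:

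- Control numerator: 0.30 × 0.60 × 0.60 + 0.70 × 0.10 × 0.20 = 0.122.
- Control counselled: 0.30 × 0.60 + 0.70 × 0.10 = 0.25, so Reading A gives 0.122 / 0.25 = 48.8%, against 32% in the intervention arm when there is no effect.
- Reading B gives 12.2% in control, against 0.80 × 0.32 = 25.6%.

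If counselling reached the same men in both arms, both biases would vanish.

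**Interest against use.** Let 40% of non-users be interested in both arms.

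- Use rising from 22% to 30%: 0.78 × 0.40 = 31.2% falls to 0.70 × 0.40 = 28.0%, or -3.2 points. If 10% of users also want to change, 33.4% falls to 31.0%, or -2.4.
- Use rising from 25% to 45%: 30.0% falls to 22.0%, or -8.0 points; with 10% of users changing, 32.5% falls to 26.5%, or -6.0.

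**Precision under Reading A.** If 20% of control and 80% of intervention men are counselled, 840 × 0.20 = 168 and 1,680 × 0.80 = 1,344 men are analysed. Borrowing 22% versus 30% and a correlation of 0.01, power falls from 79.3% to about 45%.

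**Order of events.** Section 2.2 has the module ask about interest first, with extensive counselling following at intervention sites. Item 4b records interest after counselling. Both cannot describe the same measurement.

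**The case against.** The strongest defence is that item 4b speaks of male clients, and the counselling phrase may describe only when interest is recorded. Nothing says that uncounselled men are excluded, and the Data analysis plan states an intention-to-treat principle by facility. That stands: exclusion is one reading, not the stated rule. But the all-men reading has its own bias, because it credits the intervention for delivering counselling even when interest is unchanged. The intention-to-treat sentence speaks of women and sets no denominator for this outcome.

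A reader might infer that nearly all intervention men and few control men are counselled, or that the sign must reverse. The documents support neither. The common module prompts in both arms, and all patients receive counselling on barrier protection. The 20% counselling frequency under Preliminary data comes from 24 observed interactions of all types in 2006, which the protocol itself calls limited and non-standardised, so it does not describe the trial's control arm. Under Reading A, reversal needs selective control counselling or enough extra uptake to reduce interest.

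It is also fair that current users are asked about changing method and that dual methods are promoted, which softens the fall in interest. And men's use is not absent from the plan: Endpoints arguably already makes it primary. That sharpens the contradiction with item 4b.

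Finally, a reader might infer that the male baseline is settled at 18-45. It is not: section 1.1 says so, while the consent text covering both phases says 18 and above.

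**Conclusion.** The point holds in this form: item 4b ties the men's primary outcome to a post-randomisation event that is part of the intervention, leaves the denominator open, and contradicts Endpoints, objective 1 and the question order in section 2.2. These contradictions rest on the text alone.

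The size of any bias rests on assumed rates. For a true gain of 5 points, restriction to counselled men gives between +5 and -11.8 in the cases shown. Counting uncounselled men as not interested gives +13.4 to +19.2 when interest does not differ. The fall in interest from rising use alone is 2.4 to 8.0 points. A reversed sign is possible, not established, and the protocol does not show that an intention-to-treat comparison has been abandoned. What it does show is that the male result could not be interpreted as the outcome is now defined.

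**What to change.** - Reconcile item 4b with Endpoints. Make the men's primary outcome the proportion of all eligible men seen, counselled or not, whose couple currently uses a modern method (own condom use, vasectomy or partner's method), analysed by randomised site. Listing men's use only as secondary would demote what Endpoints already makes primary.
- If interest is kept, make it secondary. Ask it of every man at the same point in the visit in both arms regardless of counselling, use all men seen as the denominator, and report it alongside current use. Changing the denominator alone is not enough, as Reading B shows.
- Reconcile the male baseline age in section 1.1 with section 3.1 and the consent text. Then recalculate the male sample size on the same population and the same outcome as at follow-up.

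The cost is protocol wording and, if the baseline is aligned to 18 and above, slightly more baseline abstraction for men over 45. The use fields are already collected.
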